### Adverse events and safety reporting

The principles of ICH GCP require that both investigators and sponsors follow specific procedures when notifying adverse events or reactions in clinical trials. The definitions of the EU Directive 2001/20/EC Article 2 based on the principles of ICH GCP apply to this trial protocol. All adverse events will be assessed for seriousness, causality and expectedness. Causality in relation to study drug (rifampicin) is assessed as unrelated, unlikely, possible, probable or definite based on temporal relationship and clinical judgement. If the event is serious and unrelated or unlikely to be related it is classified as an SAE. If the event is possibly, probably or definitely related it is classified as a Serious Adverse Reaction (SAR). Expectedness of the adverse reaction is assessed using the
summary of product characteristics (SPC) at the time of the event. An unexpected adverse reaction is one not previously reported in the SPC, or one that is more frequent or more severe than previously reported. If a SAR is assessed as being unexpected it becomes a suspected unexpected serious adverse reaction (SUSAR). Intensity will be graded using the DAIDS toxicity scale.

The Trial Management Group at the Infectious Diseases Institute (IDI) must be notified of all grade 3-5 AEs, SAEs and SARs within 24 hours, thereafter they are responsible for reporting SAEs, SUSARs to the Sponsor, regulatory authorities and ethics committees in accordance with local regulatory and institutional guidelines.

***Interim analyses.*** Interim analysis of safety will occur after 24 participants (8 per arm) have completed the week 8 visit. The committee can modify the frequency of interim analysis and early termination could occur if the data safety committee decides there is an unacceptable level of toxicity in any of the investigational arms.

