## Abstract

**Background**: Tuberculous meningitis (TBM) has 44% (95%CI 35-52%) in-hospital mortality with standard therapy in Uganda. Rifampicin, the cornerstone of TB therapy, has 70% oral bioavailability and ~10-20% cerebrospinal fluid (CSF) penetration.  With current WHO-recommended TB treatment containing 8-12mg/kg rifampicin, CSF rifampicin exposures frequently fall below the minimal inhibitory concentration for
*M. tuberculosis*. Two Indonesian phase II studies, the first investigating intravenous rifampicin 600mg and the second oral rifampicin ~30mg/kg, found the interventions were safe and resulted in significantly increased CSF rifampicin exposures and a reduction in 6-month mortality in the investigational arms. Whether such improvements can be replicated in an HIV-positive population remains to be determined.

**Protocol**: We will perform a phase II, open-label randomised controlled trial, comparing higher-dose oral and intravenous rifampicin with current standard of care in a predominantly HIV-positive population. Participants will be allocated to one of three parallel arms (I:I:I): (i) intravenous rifampicin 20mg/kg for 2-weeks followed by oral rifampicin 35mg/kg for 6-weeks; (ii) oral rifampicin 35mg/kg for 8-weeks; (iii) standard of care, oral rifampicin 10mg/kg/day for 8-weeks. Primary endpoints will be: (i) pharmacokinetic parameters in plasma and CSF; (ii) safety. We will also examine the effect of higher-dose rifampicin on survival time, neurological outcomes and incidence of immune reconstitution inflammatory syndrome. We will enrol 60 adults with suspected TBM, from two hospitals in Uganda, with follow-up to 6 months post-enrolment.

**Discussion**: HIV co-infection affects the bioavailability of rifampicin in the initial days of therapy, risk of drug toxicity and drug interactions, and ultimately mortality from TBM. Our study aims to demonstrate, in a predominantly HIV-positive population, the safety and pharmacokinetic superiority of one or both investigational arms compared to current standard of care. The most favourable dose may ultimately be taken forward into an adequately powered phase III trial.

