### Randomisation and treatment allocation

Adults who have given consent for, and undergone, a diagnostic screening lumbar puncture and are eligible for enrolment will then be approached for enrolment consent after which they will be randomised. Randomisation will occur at study entry and must occur prior to the 4th dose of TB treatment. Participants will be randomised by a computer generated permutated block randomization algorithm of different sized blocks with a 1:1:1 randomization ratio into the three arms described above.

Randomisation will be stratified by:

1. Clinical site2. British Medical Research Council (BMRC) TBM disease grade I or II/III at time of consent

All randomised participants will initiate their allocated study TB treatment within 24 hours of randomisation, and preferably the same day. As TBM is a medical emergency, initiation of standard of care TB treatment will not be delayed whilst waiting for randomisation.

***Treatment discontinuation***. Due to the urgent need to begin TBM therapy to reduce mortality, enrolment will not be delayed whilst waiting for enrolment blood test results and participants will be replaced
*a posteriori* if baseline ALT>3x ULN. As infection with a rifampicin resistant TB strain is an exclusion criterion, all patients in whom rifampicin resistant TB is identified after randomisation may have their treatment altered as per physician judgement. Once randomised, analysis is by modified intent-to-treat (ITT).

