### Data collection

***Baseline and subsequent assessment.*** Participants will be followed as in-patients for the first 14 days and then approximately 4 weekly as outpatients until week 24, see
Table 5 and
Table 6. If a trial participant dies during the in-patient period additional consent will be sought from family members for a post-mortem examination to explore cause of death and levels of rifampicin in brain tissue. Recruitment will continue for 12–18 months with an additional 6 months follow-up period. The trial will be considered closed when the last participant has completed 24 weeks in the study, all SAEs resolved and all follow-up and laboratory reports have been received.

***Data handling and data management.*** Source documents are made up of detailed case report forms (CRFs), laboratory results, radiology results and other relevant documents. Data entry will occur via the DataFax system, whereby the paper-based case record forms are scanned, emailed to a server, and data entered by intelligent character recognition. After an initial automated error-checking, secondary review for accuracy is then performed by the DataFax team at the Infectious Diseases Institute, Uganda. The DataFax system allows for automated data queries to alert for any missing data on an ongoing basis. Second, this also allows for permanent archiving and potential remote review by oversight bodies. Study forms will be harmonized between all study sites enabling multi-site data management. The investigator will retain study essential source documents for 20-years after the completion of the study, as per Ugandan guidelines. Digital images of the source documents will be retained for an indefinite period.

***Quality control and assurance.*** Site monitoring is conducted to ensure that the human subject protection, study procedures, laboratory, study intervention administration, and data collection processes are of high quality and meet the sponsor, ICH E6 and regulatory guidelines. The study may be subject to audit by the London School of Hygiene & Tropical Medicine under their remit as Sponsor, as well as other regulatory bodies to ensure adherence to Good Clinical Practice.

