### Statistical considerations

***Sample size.*** Approximately 800 adults presenting with symptoms of meningitis will be assessed, of which it is anticipated two-thirds will have cryptococcal meningitis. The circa 240 patients with negative CSF cryptococcal antigen (crAg) will undergo a comprehensive TBM diagnostic panel (Xpert MTB/Rif, Xpert Ultra, mycobacterial growth indicator tube (MGIT) culture, and/or next generation sequencing) from which we anticipate 60 people with suspected or confirmed TBM will be recruited into the randomised trial.

The sample size is determined following the assumption that PK parameters are normally distributed on the log scale. Estimated rifampicin log-transformed C
_max_ standard deviation is taken from
*Ruslami et al*.
^1^ The global study significance level (alpha) will be 10%, which is appropriate for phase II studies. Using the Bonferonni correction for multiple testing, each individual comparison will be made with alpha of 5%. Group sample sizes of n=15 achieve 90% power to reject the null hypothesis of equal means when the log-transformed population mean difference is 0.54mg/L with standard deviation of ±0.36mg/L in the control group and ±0.48mg/L (33% higher) in the experimental group, with a significance level of 0.05 using a two-sided, two sample unequal variance t-test. If the standard deviation differs from our estimate, the overall detectable effect size at 90% power will be 1.5 times the standard deviation, and 1.27 times the standard deviation at 80% power. We will not formally compare equivalence of the two investigational arms as this would require a larger sample size. Comparison of the two investigational arms will be primarily descriptive.

This phase II study would be underpowered to detect a survival benefit unless the effect size is large. A one-sided log rank test with 20 subjects per arm provides 80% power at 0.05 significance to detect a hazard ratio of 0.285 when 40% of controls survive 8-weeks. This assumes no more than 1 person drops out or is lost to follow-up per arm. The prior lost to follow up rate has been <1% in recent Ugandan meningitis trials.

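### The only scheduled interim safety analysis is triggered by completed week 8 visits, so read literally it counts survivors and comes later as early deaths rise

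*Protocol article*

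**What the plan says.** Under Adverse events and safety reporting (Interim analyses), the protocol article states: "Interim analysis of safety will occur after 24 participants (8 per arm) have completed the week 8 visit". It continues: "The committee can modify the frequency of interim analysis and early termination could occur", the latter if the data safety committee finds unacceptable toxicity in an investigational arm. No other interim look is scheduled.

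The out-patient schedule (Table 6) makes week 8 an attended visit with history, examination, functional scoring and a hepatic panel.

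The figures that decide when the trigger is reached are elsewhere in the article:

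- Abstract: "We will enrol 60 adults with suspected TBM".
- Randomisation and treatment allocation: "with a 1:1:1 randomization ratio into the three arms", hence 20 per arm.
- Statistical considerations (Sample size): "A one-sided log rank test with 20 subjects per arm provides 80% power at 0.05 significance" for a hazard ratio of 0.285 "when 40% of controls survive 8-weeks".
- Abstract (Background): "44% (95%CI 35-52%) in-hospital mortality with standard therapy in Uganda".
- Data collection: "Recruitment will continue for 12–18 months with an additional 6 months follow-up period".

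**The concern.** The trigger depends on people being alive and attending at week 8. With 20 controls and 40% planned survival, the expected number of control completers in the whole trial is 20 x 0.40 = 8, exactly what the trigger asks of that arm. There is no margin.

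The direction is also wrong. The more participants die before week 8, from the disease or from treatment, the later the look comes. A safety review should not recede as harm increases.

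Safety is one of the two primary endpoints, and the look is the scheduled occasion on which an arm could be stopped for toxicity. If it falls when few participants remain to be randomised, stopping enrolment to an arm at that point spares few people.

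**Working it through.** **Inputs from the article.** 60 participants, 20 per arm; trigger of 8 week 8 completers per arm; control survival 40% at 8 weeks; hazard ratio 0.285; 44% in-hospital mortality (interval 35 to 52%); recruitment over 12 to 18 months. The section Rifampicin in TBM adds 8-week mortality of 24% versus 55% in the cited intravenous study.

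**Assumptions.** Even accrual, permuted blocks of 3 and 6, an 8-week lag, every survivor attends, and no replacement of participants. In-hospital mortality stands in for 8-week mortality.

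**Step 1: is 40% survival the planning value actually used?** Under proportional hazards, experimental survival is 0.40^0.285 = 0.77. Expected deaths with 20 per arm are 20 x 0.60 + 20 x 0.23 = 16.6. Schoenfeld power, one-sided 0.05, is Phi(sqrt(16.6/4) x |ln 0.285| - 1.645) = Phi(0.91) = 82%. With 19 per arm (one drop-out each) it is 80%, the stated figure. Reading the 40% as deaths gives 66%. So 40% survival is no slip.

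**Step 2: chance that the per-arm trigger is ever met.** With S ~ Bin(20, s):

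- s = 0.40: P(S >= 8) = 0.584. At s = 0.77 it is practically 1, so for 40/77/77% the trigger is never met with probability 1 - 0.584 = 0.416.
- s = 0.56 in all arms: 0.952^3 = 0.862; never met 0.138.
- s = 0.65 in all arms: 0.994^3 = 0.982; never met 0.018.

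**Step 3: how many are randomised when the look falls.** Accrual is 60/18 = 3.3 to 60/12 = 5 per month. Eight weeks is 1.84 months, so about 6 to 9 more are randomised during the wait. Simulation gives the following, with medians among runs in which the trigger is met. The first median is for 12 months of accrual and the second for 18.

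| Survival (control / experimental arms) | 8 per arm: never met | 8 per arm: median randomised | 24 pooled: median randomised |
|---|---|---|---|
| 40 / 77 / 77% (sample size section) | about 41% | 58 or 55 | 46 or 43 |
| 45 / 76 / 76% (cited intravenous study) | about 25% | 56 or 53 | 46 or 43 |
| 56% in all arms (44% mortality) | about 14% | 57 or 54 | 52 or 49 |
| 65% in all arms (35% mortality) | about 2% | 51 or 48 | 46 or 43 |
| 48% in all arms (52% mortality) | about 44% | 60 or 59 | 58 or 55 |

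Repeat runs move the medians by about one participant.

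**Step 4: hand check of the pooled column.** For 40/77/77%, mean survival is (0.40 + 0.77 + 0.77)/3 = 0.647. Then 24/0.647 = 37, plus 6 to 9 gives 43 to 46. For 56%, 24/0.56 = 43, plus 6 to 9 gives 49 to 52.

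**Step 5: the same look if deaths before week 8 count.** The first 24 randomised reach week 8 or an earlier end when 24 + 6 to 9 = 30 to 33 are randomised. Simulation gives medians of 33 and 30, and the look always occurs.

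**The case against.** Four points can fairly be made against this.

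- **Other safeguards exist.** The committee may change the frequency of analysis. All grade 3-5 events, serious adverse events and serious adverse reactions must reach the Trial Management Group within 24 hours, and hepatic panels are scheduled well before week 8. This stands. A reader might infer that the plan leaves participants unprotected until the look, and the article does not support that. But 24-hour reporting passes on individual events and is not a between-arm review, and the discretion fixes no earlier date.
- **The bracketed 8 per arm may only describe 24 people under equal allocation.** If 24 pooled completers suffice, the look falls at roughly 42 to 52 of 60 in every scenario except 48% survival, and it is almost always reached. So the sizeable chance of no look depends on the literal per-arm reading. The pooled reading still puts the look after at least two thirds of randomisation.
- **The 40% is a power input for controls and the harshest survival figure available.** This also stands. A reader might divide 24 by 0.40 and conclude that all 60 must be randomised, but the article gives that rate for controls only. The milder figures are shown for this reason, and at 65% survival the literal trigger is almost always met, at 48 to 51 of 60.
- **The full protocol or committee charter may say how early deaths count.** Possibly. The point here is not missing detail, because the article states a trigger and that trigger performs badly as worded.

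**Conclusion.** The concern holds for the scheduled look as worded. The literal trigger recedes as early deaths rise, whatever the mortality rate. At the sample size section's own survival figures it is never met with probability about 42%, and otherwise falls with a median of 55 to 58 of 60 randomised. Under 44% mortality in all arms the figures are about 14% and 54 to 57; under 35% mortality, about 2% and 48 to 51.

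These sizes rest on even accrual, full attendance by survivors and the per-arm reading. Missed visits would delay the look further. The pooled reading brings it forward, and counting early deaths as completed follow-up removes the problem.

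The conclusion does not extend to saying that the trial has no other safety oversight or that no earlier look could take place. It is that the one look the plan fixes is tied to the wrong count.

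**What to change.** Reword the trigger in the protocol, and match it in the safety committee's charter: hold the interim safety analysis once the first 24 randomised participants (about 8 per arm) have each completed week 8 or have died, withdrawn or been lost before it. Include all events from all randomised participants up to that data cut. If the sponsor already intends this, the sentence should say so.

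The cost is one sentence in each document and an earlier data cut. The downside is that fewer participants with complete 8-week follow-up contribute. Of the first 24, about 8 x (0.40 + 0.77 + 0.77) = 16 would be week 8 survivors at the sample size section's figures, or 24 x 0.56 = 13 at 44% mortality, instead of 24. The deaths and other early events among the rest would be included, and they are what a safety review needs to see. No stopping threshold is proposed.

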### Data collection

***Baseline and subsequent assessment.*** Participants will be followed as in-patients for the first 14 days and then approximately 4 weekly as outpatients until week 24, see
Table 5 and
Table 6. If a trial participant dies during the in-patient period additional consent will be sought from family members for a post-mortem examination to explore cause of death and levels of rifampicin in brain tissue. Recruitment will continue for 12–18 months with an additional 6 months follow-up period. The trial will be considered closed when the last participant has completed 24 weeks in the study, all SAEs resolved and all follow-up and laboratory reports have been received.

***Data handling and data management.*** Source documents are made up of detailed case report forms (CRFs), laboratory results, radiology results and other relevant documents. Data entry will occur via the DataFax system, whereby the paper-based case record forms are scanned, emailed to a server, and data entered by intelligent character recognition. After an initial automated error-checking, secondary review for accuracy is then performed by the DataFax team at the Infectious Diseases Institute, Uganda. The DataFax system allows for automated data queries to alert for any missing data on an ongoing basis. Second, this also allows for permanent archiving and potential remote review by oversight bodies. Study forms will be harmonized between all study sites enabling multi-site data management. The investigator will retain study essential source documents for 20-years after the completion of the study, as per Ugandan guidelines. Digital images of the source documents will be retained for an indefinite period.

***Quality control and assurance.*** Site monitoring is conducted to ensure that the human subject protection, study procedures, laboratory, study intervention administration, and data collection processes are of high quality and meet the sponsor, ICH E6 and regulatory guidelines. The study may be subject to audit by the London School of Hygiene & Tropical Medicine under their remit as Sponsor, as well as other regulatory bodies to ensure adherence to Good Clinical Practice.

### Statistical considerations

***Sample size.*** Approximately 800 adults presenting with symptoms of meningitis will be assessed, of which it is anticipated two-thirds will have cryptococcal meningitis. The circa 240 patients with negative CSF cryptococcal antigen (crAg) will undergo a comprehensive TBM diagnostic panel (Xpert MTB/Rif, Xpert Ultra, mycobacterial growth indicator tube (MGIT) culture, and/or next generation sequencing) from which we anticipate 60 people with suspected or confirmed TBM will be recruited into the randomised trial.

The sample size is determined following the assumption that PK parameters are normally distributed on the log scale. Estimated rifampicin log-transformed C
_max_ standard deviation is taken from
*Ruslami et al*.
^1^ The global study significance level (alpha) will be 10%, which is appropriate for phase II studies. Using the Bonferonni correction for multiple testing, each individual comparison will be made with alpha of 5%. Group sample sizes of n=15 achieve 90% power to reject the null hypothesis of equal means when the log-transformed population mean difference is 0.54mg/L with standard deviation of ±0.36mg/L in the control group and ±0.48mg/L (33% higher) in the experimental group, with a significance level of 0.05 using a two-sided, two sample unequal variance t-test. If the standard deviation differs from our estimate, the overall detectable effect size at 90% power will be 1.5 times the standard deviation, and 1.27 times the standard deviation at 80% power. We will not formally compare equivalence of the two investigational arms as this would require a larger sample size. Comparison of the two investigational arms will be primarily descriptive.

This phase II study would be underpowered to detect a survival benefit unless the effect size is large. A one-sided log rank test with 20 subjects per arm provides 80% power at 0.05 significance to detect a hazard ratio of 0.285 when 40% of controls survive 8-weeks. This assumes no more than 1 person drops out or is lost to follow-up per arm. The prior lost to follow up rate has been <1% in recent Ugandan meningitis trials.

***Statistical methods.*** After data cleaning, analysis will proceed according to the pre-specified analysis plan using Stata version 13. The trial will be reported in accordance with CONSORT guidelines and primary analyses will be conducted by the participant’s originally assigned group (ITT). Analyses will be conducted on individuals from both study sites together and all analyses will be adjusted for site, BMRC grade and any baseline variables associated with missingness of the analysis outcome.

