### Endpoints

***Primary end points***

*1. Pharmacokinetic parameters*

Plasma and CSF rifampicin area under the curve (AUC
_0-24h_), and maximum concentration (C
_max_)

*2. Adverse events*

We will use a composite safety endpoint for the 8-week intervention period that includes clinical grade 3-5 adverse events (AEs) (as classified by Division of AIDS (DAIDS) Toxicity Scale) or all serious adverse events (SAEs), drug-induced liver injury (DILI), grade 3-5 defined by alanine transaminase (ALT) >5x upper limit of normal (ULN), or discontinuation of rifampicin for >5 consecutive days in the first 8 weeks for any cause.

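### The 5% per-comparison level secures the stated 10% global alpha for one PK parameter only, but four are listed as primary with no lead parameter or order

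*Protocol article*

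**What the plan says.** Under Statistical considerations (Sample size), the Protocol article fixes the overall error rate: "The global study significance level (alpha) will be 10%, which is appropriate for phase II studies". It then gives the rule meant to deliver that rate: "Using the Bonferonni correction for multiple testing, each individual comparison will be made with alpha of 5" per cent. The same section leaves the comparison between the two investigational arms to description, so two formal arm comparisons remain, each against control.

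The sizing is for one parameter. The standard deviation is that of log-transformed Cmax, and the section does not say whether this is plasma or CSF. The inputs are a log-scale difference of 0.54 and SDs of 0.36 (control) and 0.48 (experimental), tested by a two-sided Welch t-test at 5%. The result reported is: "Group sample sizes of n=15 achieve 90% power to reject the null hypothesis of equal means".

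Under Primary end points, the PK endpoint is wider. Its entry opens with "Plasma and CSF rifampicin area under the curve". Cmax in the same two fluids is listed beside it, which makes four parameters. The primary hypothesis is also worded in terms of significant increases in both plasma and CSF. The Pharmacokinetic analysis section says which parameters will be calculated. It does not say which one carries the confirmatory test.

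**The concern.** The article claims familywise control at 10% and prints the rule for achieving it. The divisor of 2 is used up by the two arm comparisons, so nothing is left for more than one parameter. With four parameters given equal primary standing, a significant result on any one of them could be reported as PK superiority, and the overall chance of a false claim would then exceed 10%.

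The Introduction says the study aims to show PK superiority of one or both investigational arms, so that the most favourable dose can go to phase III. The error rate attached to that claim should be the one stated. The level is already a lenient one, chosen because this is phase II, so there is little room for further slippage.

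**Working it through.** **1. The plan's own alpha.** Two comparisons at 5%: 0.05 + 0.05 = 0.10, as stated. If they were independent, the error would be 1 - 0.95^2 = 9.75%. They share a control arm, and simulation (Welch tests, 15 per arm, no true difference) gives about 9%. So the 10% holds for one parameter.

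**2. The plan's own power.** Inputs from the Sample size section: n = 15 per group, difference 0.54, SDs 0.36 and 0.48 on the log scale, two-sided 0.05.
- Standard error = sqrt(0.36^2/15 + 0.48^2/15) = sqrt(0.1296/15 + 0.2304/15) = sqrt(0.0240) = 0.155.
- Noncentrality = 0.54/0.155 = 3.49. Welch degrees of freedom are about 26 and the critical t is 2.06.
- Noncentral-t power = 91.8%. With 14 per group it is 89.8%, so 15 is the smallest n that reaches 90%. The stated figure reproduces.

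**3. More than one parameter, any significant one counting as success.** Simulation: three arms of 15 with a shared control, two-sided Welch tests at 5% for each investigational arm versus control, equal variances, no true difference on any parameter. The correlations between parameters are assumptions, because the article gives none.

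| Parameters tested | Assumed correlations | Familywise error |
|---|---|---|
| One | none needed | about 9% |
| Plasma AUC and Cmax | 0.99 / 0.9 / 0.7 | 10% / 12% / 15% |
| Those two plus one CSF measure | plasma pair 0.9 / 0.7; CSF with plasma 0.5 | 19% / 21% |
| All four | 0.99 throughout | 11% |
| All four | 0.95 within matrix, 0.9 between | 16% |
| All four | 0.9 within, 0.7 between | 20% |
| All four | 0.7 within, 0.3 between | 26-27% |
| All four | 0 | 31% |

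In the three-parameter row, raising the plasma correlation to 0.99 gives 17%. Every setting with more than one parameter exceeds 10%, although two plasma parameters correlated at 0.99 do so only barely.

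**4. How many tests are feasible.** Four parameters by two arms is eight tests. The Pharmacokinetic sampling paragraph gives one CSF sample around day 2, and the notes to the in-patient schedule randomise its timing to one interval after the dose. The two-stage calculation is limited to participants with a complete concentration curve. One CSF sample does not give a participant-level AUC or Cmax, so eight is an upper count. The rows for two or three parameters may be nearer to what can be done.

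**5. Cost of spreading alpha instead.** 0.10/8 = 0.0125 per test. With the inputs of step 2, power at 15 per group falls from 91.8% to 78.1%. Reaching 90% needs 20 per group, which gives 91.1% and requires every one of the planned 20 per arm to be evaluable.

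**The case against.** The strongest reply is that nothing printed is wrong in its own setting. The phrase about individual comparisons sits in a paragraph about arms, sized on Cmax, and there 10%/2 = 5% is correct. The article does not say that all four parameters get a formal 5% test, and it refers to a pre-specified analysis plan that is not shown, which could name the lead parameter. That part stands: formal testing of all four is an inference. It does not remove the point, because the article itself fixes a global error rate, a correction and a resulting level, and also lists four co-equal primary parameters. The printed rule does not secure the printed rate for that list.

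A second reply is that the primary hypothesis joins plasma and CSF. If success needed every parameter to be significant, there would be no inflation. That is true, but no such rule is written. Under it, the stated 90%, computed for Cmax alone, would not be the power for success.

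A third reply is that the case of no difference on any parameter is remote, since the Introduction reports roughly threefold exposure from a smaller dose increase than those studied here. This is fair and limits the practical harm. The choice between the investigational arms is also left to description and depends on safety as well, so these tests do not by themselves pick a dose.

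A reader might infer something stronger: that eight tests are planned and that the true familywise error is 16-34%. The documents do not support that. The 34% is 1 - 0.95^8 = 33.7%, which ignores the shared control (31% with it, even at zero correlation). The 16% belongs to one assumed correlation pattern and is not a floor. The single CSF sample makes the count of eight doubtful. Nor is the safety composite a reason to enlarge the family: the article assigns it no alpha and it supports no superiority claim.

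**Conclusion.** The point holds in a limited form. The 5% level protects the 10% global alpha for one PK parameter (about 9% simulated), and the protocol lists four without saying which one that is. If any significant parameter counts as success, the error is about 10-15% for the plasma pair, about 19-21% with one CSF measure added, and about 11-31% for all four. These figures depend on that success rule, on the assumed correlations and on no true difference anywhere. The direction is secure; the size is not, and no single figure should be quoted as the trial's actual error rate. It is worth correcting because the sponsor chose to claim familywise control and the repair is small.

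**What to change.** State which parameter the 5% test applies to. Name one plasma PK parameter as the confirmatory test for each investigational arm against control at 5%: plasma Cmax, if that is the parameter that was powered, or plasma AUC0-24h with the power calculation restated for it. Test the remaining parameters in a fixed order at 5% within each arm, stopping at the first non-significant result, or label them secondary. Each arm then spends at most 5%, the two arms together at most 10%, and the lead test, if it is Cmax, keeps its power of about 92% at 15 per group. The order should include only CSF quantities that the single-sample design can estimate.

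The cost is a paragraph in the protocol or analysis plan, written before any outcome data are examined, and no extra participants. The one drawback is that later parameters carry confirmatory weight only if the earlier ones succeed.
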